**Inclusion criteria**
1. Adult patients (age ≥ 18 years old)
2. Admitted to ICU
3. Invasive mechanical ventilation for at least 48 hours
4. Presence of clinical criteria for VAP, defined as: a. Temperature > 38°C or < 36°C **OR** leucocyte > 12,000/mL or < 4,000/mL or > 10% immature forms **AND** b. New onset of purulent tracheal secretions **OR** change in secretion characteristics **OR** increase in secretions volume **OR** increased suctioning requirements
5. Lower respiratory tract microbiological sample under analysis or collection on the day of trial triage
6. Chest imaging (chest X-ray or computed tomography) on the day of trial triage

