**Exclusion criteria**
1. Pregnancy or active lactation
2. Current use or indication of use of systemic antibiotics for any reasons
3. Hemodynamic instability, defined as new-onset hypotension unresponsive to fluid boluses or increase in vasopressor dose > 0.1mcg/kg/minute of norepinephrine or equivalent in the previous 6 hours
4. Worsening gas exchange, defined as an increase in the oxygen-inspired fraction ≥ 20% or an increase in PEEP ≥ 3cmH_2_O after a period of stability of ≥ 2 days
5. Prolonged mechanical ventilation, defined as an invasive mechanical ventilation duration ≥ 21 days
6. A new pulmonary opacity on chest image suggestive of new infectious infiltrates
7. Previous pulmonary disease that hampers the radiographic interpretation for VAP diagnosis
8. Previous diagnosis of VAP during hospitalization
9. Neutropenia (absolute neutrophil count < 1,000/mL)
10. Severe known immunosuppression
11. Tracheostomy on the day of trial triage
12. Prior inclusion in the trial in the last 30 days
13. Expected withholding or withdrawing of life support within 7 days
14. Patients unlikely to survive > 48 hours
15. Consent refusal to participate in the trial

ICU - intensive care unit; VAP - ventilator-associated pneumonia; PEEP - positive end-expiratory pressure.

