### Trial treatments

Figure 2 presents the main elements of the trial protocol. In the Watchful Waiting Group, participants will not receive antimicrobials for VAT. Antimicrobials can be used, however, at the clinician’s discretion when other non-VAT-related indications ensue, such as progression to VAP, hemodynamic worsening or shock, newly confirmed or highly probable infection by the treating physician, unexplained new or worsened organ dysfunction or any other validated clinical indication for antimicrobial utilization. Antimicrobial initiation is not advised if lower respiratory tract cultures are positive and the patient does not develop other treatment indications.

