### Statistical analysis

The main analysis will follow the intent-to-treat framework, where the null hypothesis is that the number of VFDs up to 28 days in the Watchful Waiting Group is less than the number of VFDs in the Antibiotic Treatment Group for 7 days by a margin of 20%. If the upper bound of the 95% confidence interval for inferiority of the Watchful Waiting Group is < 20%, we will reject the null hypothesis of inferiority. To estimate the effect of treatment on the primary outcome, as well as in the interim analyses, an appropriate statistical model adjusted for stratification variables will be used for this type of outcome according to the variable behavior: either a generalized additive model for location scale and shape with zero-inflated beta distribution or nonparametric tests with the calculation of measures of effect and confidence intervals using resampling techniques (bootstrap) can be used. The effect size will be estimated according to the model best fitted to the data, with a 1-sided 95% confidence interval (95%CI) for noninferiority. If the noninferiority hypothesis is satisfied, superiority for the primary outcome will be tested considering a 95%CI using a hierarchical closed testing procedure. A primary sensitivity analysis of this noninferiority analysis will be a per-protocol analysis. Although per-protocol analyses are usually the primary analysis framework recommended for noninferiority trials, the intention-to-treat analysis framework may lead to more conservative estimates in antimicrobial trials.^(29)^ A p value of 0.05 will be considered to indicate statistical significance in the final analysis.

We also performed preplanned sensitivity analyses of the primary outcome, including only patients with microbiologically confirmed VAT, and we analyzed the randomization groups as an instrumental variable. Preplanned subgroup analyses will include the following: patients with or without a diagnosis of coronavirus disease 2019 (COVID-19) or other viral pneumonia, age ≤ 60 or > 60 years old, diagnosis of trauma on admission, acute brain injury, invasive mechanical ventilation duration of ≤ 5 or > 5 days at the time of randomization and effective vs. ineffective empirical antimicrobial treatment for isolated pathogens.

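### The subgroup by effectiveness of empirical treatment is named by treatment received after randomisation, given for VAT in one arm only, so as named it supports no valid randomised comparison

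*Protocol article*

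**What the plan says.** The protocol article, under Statistical analysis, introduces a list with "Preplanned subgroup analyses will include the following". The entries are viral pneumonia including COVID-19, age, trauma on admission, acute brain injury, "invasive mechanical ventilation duration of ≤ 5 or > 5 days at the time of randomization", and finally "effective vs. ineffective empirical antimicrobial treatment for isolated pathogens".

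Four other statements bear on that last entry:

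- Table 1, exclusion criterion 2, bars "Current use or indication of use of systemic antibiotics for any reasons".
- Trial treatments: "In the Watchful Waiting Group, participants will not receive antimicrobials for VAT". Antimicrobials may be used in that arm "when other non-VAT-related indications ensue, such as progression to VAP", and the section adds that "Antimicrobial initiation is not advised if lower respiratory tract cultures are positive and the patient does not develop other treatment indications".
- Trial treatments and Protocol deviations: in the antibiotic arm the regimen follows randomisation (a start later than 24 hours is a deviation) and is adjusted once microbiology is available.
- Table 1, inclusion criterion 5, requires in every patient a "Lower respiratory tract microbiological sample under analysis or collection on the day of trial triage".

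The article gives no rule for placing Watchful Waiting patients in either level of this subgroup. It leaves the details of subgroup analyses to the SAP.

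**The concern.** A subgroup analysis of a randomised trial compares the arms within levels of a factor that allocation cannot have influenced. The first five entries describe the patient. The sixth describes what was done to the patient after allocation and how well it matched the organism. In one arm that treatment is withheld by design.

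What is at stake is the reading of a natural clinical question, namely whether antibiotics help when they cover the organism. The article says that the results should inform guidelines. A table that shows this factor beside true baseline subgroups would lend it the authority of a randomised comparison that it does not have.

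**Working it through.** The plan attaches no number to this subgroup, so there is no figure to reproduce. The check is on timing and arm membership.

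**1. Is the factor known at randomisation?** Exclusion criterion 2 removes anyone already on systemic antibiotics or with an indication for them, so no patient in either arm has an empirical regimen at entry. In the antibiotic arm the regimen is started after randomisation, and its match to the pathogen can be judged only when cultures return. The factor is post-randomisation in both arms.

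**2. In which arm does it exist?** For VAT treatment, only in the antibiotic arm. The planned size is 295 per group, so the factor is undefined for VAT treatment in 295 / 590 = 50% of planned patients. In the antibiotic arm it exists only where a pathogen was isolated.

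**3. Can Watchful Waiting patients be classified another way?** Only through a later antimicrobial start. Trial treatments allows this for VAP, haemodynamic worsening, new organ dysfunction, another infection or another valid indication. Protocol deviations and the Discussion also foresee starts without such an indication. All these routes are post-randomisation and selected, and a positive culture alone is not meant to trigger one. The patients so classified are not the counterparts of antibiotic-arm patients in the same level.

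**4. What follows?** With one arm empty in each level, no within-level contrast or interaction can be estimated. With that arm filled by later starters, the contrast is no longer protected by randomisation.

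**5. How large could a spurious difference be?** The documents cannot say. As an illustration only, compare each level of the antibiotic arm with all Watchful Waiting patients, with no true treatment effect. From the article: SD of ventilator-free days (VFDs) 10.67. Assumed, not in the documents:

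- a standard normal prognosis score s, higher being worse, correlated −0.3 with VFDs;
- log-odds of ineffective therapy = −0.85 + b·s, which gives about 30 to 33% ineffective.

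Then

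difference from Watchful Waiting = −0.3 × 10.67 × (mean of s in the level) = −3.201 × (mean of s)

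The mean of s comes from numerical integration over the score.

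| b | mean s, effective | difference, effective | mean s, ineffective | difference, ineffective |
|---|---|---|---|---|
| 0 | 0 | 0.0 | 0 | 0.0 |
| 0.3 | −0.089 | +0.3 | 0.205 | −0.7 |
| 0.5 | −0.147 | +0.5 | 0.329 | −1.1 |
| 1.0 | −0.277 | +0.9 | 0.561 | −1.8 |

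Differences are in VFDs; positive favours antibiotics. For b = 1.0: −3.201 × (−0.277) = +0.89 and −3.201 × 0.561 = −1.80.

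The article's margin is 1.5 VFDs (20% of 7.69 = 1.538). Under the strongest assumed link, one level shows a false difference beyond that margin. With no link there is none. The sign is opposite in the two levels.

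**The case against.** The strongest defence is that the article gives one phrase and defers the definition to the SAP, which is not shown. The SAP may classify both arms by susceptibility to the unit's regimen, or confine the analysis to the antibiotic arm. This stands as far as nobody can say from the article which analysis will be run. It does not remove the point. The article names the variable, and that variable is treatment. A SAP that made the analysis valid would have to put a different, baseline-anchored variable in its place.

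A second objection stands in full: a reader might infer that no randomised comparison near this label is possible. The documents do not support that. The respiratory sample is required at entry in both arms, and the empirical choice is tied to each unit's microbiota.

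A reader might also infer that the classified Watchful Waiting patients are all failures of watchful waiting, so that the subgroup must favour antibiotics. That goes too far. Starts for an unrelated infection, or as protocol deviations driven by clinician preference, need not reflect deterioration. The direction also depends on the comparator and the level, as the table shows.

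Finally, this is one of six subgroups, and the Discussion presents the trial as one of treatment strategies. That limits the weight of the point.

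**Conclusion.** The point holds for the subgroup as named. It is defined by a post-randomisation treatment that the protocol gives for VAT in one arm only, so it yields no valid randomised contrast or interaction. This rests on the article's own eligibility, treatment and deviation rules and needs no outside figure.

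The size of any bias is not established. The illustration shows false differences from 0 to about +0.9 VFDs in the effective level and from 0 to about −1.8 in the ineffective level, under assumptions that the documents do not supply. Nor can one count the Watchful Waiting patients who would be classified. A reader might apply a guessed share of later antibiotic starts to the 295, but no such share is given, and the restriction to isolated pathogens would lower the count further.

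The matter should be corrected before the analysis. The primary analysis and the sample size are untouched.

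**What to change.** Do one of the following in the SAP, which the article says will be published before database closure.

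1. **Remove** the item from the randomised subgroup analyses.
2. **Redefine** it in both arms from information that allocation cannot affect: whether the pathogen isolated from the triage respiratory sample is susceptible to the unit's predefined empirical regimen. Where a centre has no regimen of its own, use the trial-supplied guideline choice, reduced to one stated regimen per centre without reference to allocation. Restrict the analysis to patients with an isolated pathogen, or make culture-negative a separate level. Test the treatment-by-subgroup interaction on that variable.

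Under either option, report the effectiveness of the treatment actually given only within the antibiotic arm, as a descriptive and non-randomised result.

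The cost is modest. Cultures are already recorded daily, and an analysis restricted to microbiologically confirmed VAT is already planned. What is added is a record of each unit's regimen, retrieval of susceptibility results and some classification work, including for patients already enrolled. The analysable set will be smaller than the full trial, so the interaction estimate will be imprecise and should be presented as such.

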### Ethics and dissemination

Participants will not be capable of providing consent due to their clinical condition (use of IMV). Therefore, consent will be obtained from their next-of-kin and/or legal representative. Given the timeliness of the intervention, participants can be randomized, and consent can be obtained within 48 hours after their inclusion in the trial. The trial is designed according to the guidelines for good clinical practice and follows the principles of the *Documento das Américas*, and it was approved by the *Hospital Sírio-Libanês* Ethical Committee (CAAEE 48749421.0.1001.5461) and by the research ethical committees of all participant sites.

Confidentiality will be ensured throughout the entire process, from data collection to data management. Only unidentifiable data will be shared.

The trial will be submitted for publication after completion, irrespective of its findings. We aim to publish the results in a high-visibility general journal and present it at critical care and infectious disease conferences for dissemination. The data generated from this trial will be made available upon request to the trial’s Steering Committee with a scientifically sound research proposal.

## DISCUSSION

The VATICAN is a large multicenter, randomized clinical trial evaluating whether VAT, in the absence of signs of septic shock or high-risk criteria for VAP, should be treated. Given its open-label nature, it should be viewed as a trial of antibiotic treatment strategies, not of antibiotic treatment itself. These results are likely to inform future guidelines about this condition.

When designing the VATICAN trial, the investigators examined essential issues that merit discussion. The most fundamental issue was designing a trial that enhanced the recruitment of centers on both ends of the equipoise for this trial, i.e., both elements for those who feel strong about routinely treating VAT and those who feel strongly about not treating VAT except in exceptional circumstances.

The VATICAN was initially considered an efficacy superiority trial of the 7-day treatment arm, given the current guideline recommendations not to treat VAT routinely. However, after discussion within the trial Steering Committee, the feedback obtained from likely participating centers, and considering the currently published evidence that treatment is commonly introduced, we decided that noninferiority hypothesis testing would be more likely to provide evidence beyond a reasonable doubt, especially for physicians who feel strongly about treating VAT. Robust evidence is essential if a clinical trial ultimately aims to change clinical practice. Since the noninferiority hypothesis led to a larger sample size, if any of the arms perform better than others, an efficacy analysis can be conducted using standard frequentist approaches and acceptable type I error rates.

Blinding and the choice of antimicrobial agent within each site are also concerns. Given the varying microbiology of lower respiratory tract infections in Brazilian ICUs,^(30)^ it was unlikely that a single antimicrobial treatment strategy would be appropriate for all participating sites. Furthermore, such a tactic would not represent the sites’ clinical practice and would ultimately hamper trial generalizability. Therefore, we decided that the best design strategy would be an unblinded design where the choice of antimicrobial agent is left to the trial site according to local antimicrobial resistance patterns. This strategy poses additional challenges in trial implementation but increases uptake of the intervention and center recruitment. In contrast, how antimicrobials are prescribed will not be monitored due to the pragmatic nature of the delivery of the intervention, although this may be a potential limitation.

Participant recruitment into was another concern during the trial design. Unpublished Brazilian data suggest that a vast majority of invasively ventilated ICU patients undergo antimicrobial treatment for a long duration of their stay. When recruiting sites, we reinforce the commitment of individual sites to the rational use of antimicrobials, which could be viewed as a positive unintended consequence of the trial. As recruitment rolls out, this is a critical planned part of site visits to optimize recruitment.

Another pitfall in the trial is the adherence to the interventions, given its unblinded nature and how strongly individual clinicians may feel regarding antimicrobial therapy, where clinicians are usually biased toward using antimicrobial therapy more than necessary for many reasons.^(31)^ This issue will be specifically monitored during the trial roll-out by evaluating the separation between treatment groups in accordance with antibiotic treatment during the first seven days after randomization. To reduce the potential biases in the final analysis, we reinforced the adjudication of protocol deviations with clear criteria, such as those described above. Treatment duration is another design choice of our trial. We chose 7 days of treatment in the routine treatment arm to allow physiological separation from the Watchful Waiting Group, but we do not consider it a protocol deviation if the treatment is shortened to 5 days in patients with full clinical improvement. Shorter (3 days) treatment durations have been suggested, but these are not currently standard practice in Brazilian ICUs.

Finally, the choice of the primary outcome was another important issue in trial design. While the incidence of VAP may be seen as an interesting outcome for the VATICAN trial, recent trials assessing VAP as a primary outcome have not shown benefits in other clinical outcomes when VAP is prevented,^(32,33)^ suggesting that VAP may be best viewed as a surrogate endpoint that is not necessarily related to other clinical outcomes. Therefore, we chose VFDs as our primary outcome, which would balance the benefits and harms of the intervention in a single, more patient-centered, composite outcome. Additionally, other secondary outcomes, such as antibiotic-free days and ICU-free days, will provide additional elements for assessment of the benefits and harms of treatment regimens.

### Perspective

As we wrote the draft for this protocol, more than 180 patients were included in the trial, and 32 sites have been trained and recruited since June 2022. With up to 50 active sites, we expect the trial to be completed by 2026. However, the above-described pitfalls and barriers to recruitment may lead to slower recruitment rates, which will be addressed by the trial Management Committee.

## CONCLUSION

The VATICAN trial represents a considerable effort to evaluate a long-standing research question that has not yet been addressed by adequately powered multicenter randomized trials. The results are likely to be immediately applicable to the bedside upon trial completion and will provide information with a low risk of bias for guideline development.
